
### Methodology for PBM application

2.12

Patients form Group 2 will receive laser treatment (photobiomodulation) in order to modulate orthodontic movement and act on inflammation and pain. The procedures will be performed immediately after the application of forces (placement of elastic bandages) on the tooth, as described:

The irradiations will be performed with a diode laser emitting infrared wavelength (Therapy XT - ANVISA RDC Standard 185/2001 - DMC, São Paulo, SP, Brazil). The power output of this equipment is 100 mW and the wavelength used will be 808 nm (±10 nm). The optical fiber diameter of the device is 600 μm, therefore a spot (area) of 0.002826 cm^2^. The energy delivered per point will be 1J. This will require a irradiation of 10 seconds per point. As 10 points will be irradiated, the total application time will be 100 seconds and the total energy delivered will be 10J. The energy density will be 25 J/cm^2^ and the power density will be 35.38 W/cm^2^ (Table 1).^[40]^The laser tip will be positioned perpendicular to the edge in direct contact with the vertical tooth mucosa, 10 seconds per site: 5 points per buccal and 5 points per lingual: 2 points, mesial and distal, in what would be considered the cervical third of the root; a central point in the middle third, and 2 points, mesial and distal, which would be equivalent to the apical third of the root (Fig. 2).During laser application both, patient and operator, will wear security goggles adequate to laser wavelength.The laser will be applied immediately after orthodontic force application (T0), 3 (T1) and 7 (T2) days later. After 30 days, the elastomeric ligature will be changed (therefore, renewal of the vertical force) and this same protocol will be applied (at times T0, T1 and T2). This same elastic bandage change will also occur 60 days after the mini-implant installation, and again the laser application protocol will be followed. Finally, 90 days after baseline, the mini-implant will be removed, as will the lingual button of the molar mesial, but without further laser application.

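### Section 2.12 states an energy density of 25 J/cm², but its own power, spot area, time and energy give about 354 J/cm²

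*Protocol article*

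**What the plan says.** All the figures come from section 2.12 (Methodology for PBM application) of the protocol article.

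- Power: "The power output of this equipment is 100 mW".
- Spot: "The optical fiber diameter of the device is 600 μm, therefore a spot (area) of 0.002826 cm^2".
- Energy per point: "The energy delivered per point will be 1J".
- Time per point: "This will require a irradiation of 10 seconds per point".
- Session totals: "As 10 points will be irradiated, the total application time will be 100 seconds and the total energy delivered will be 10J".
- Densities: "The energy density will be 25 J/cm^2^ and the power density will be 35.38 W/cm^2".

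The tip is held "in direct contact with the vertical tooth mucosa, 10 seconds per site". The text gives no second beam area, no distance between tip and tissue, and no other area over which the energy is averaged. The sham description in the same section repeats the 10 s per point and the 100 s in total. Table 1 holds the laser parameters, but its content is not shown in the text available for review.

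**The concern.** Energy density is power density multiplied by exposure time. The sentence that gives both densities therefore fixes the exposure time implicitly, and that time is not the 10 s stated just before it. At least one figure in the description of the active treatment must be wrong.

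Active versus simulated laser is the only planned difference between the two arms, and the Introduction itself makes the benefits of photobiomodulation depend on using suitable laser parameters. If the text stands, the trial would report a fluence that its own power, spot and time contradict by an order of magnitude. A reader who wants to replicate the treatment, or to place it among other fluences, could not tell which figure to use. The discrepancy would apply to each of the nine planned active sessions (three time points in each of three monthly cycles).

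**Working it through.** **Inputs (all from section 2.12):** power P = 100 mW = 0.1 W; fibre diameter d = 600 μm = 0.06 cm; spot area A = 0.002826 cm²; time t = 10 s per point; energy E = 1 J per point; 10 points; stated power density 35.38 W/cm²; stated energy density 25 J/cm².

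**Figures that reproduce**

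1. Area: π(d/2)² = π × 0.03² = 0.002827 cm²; with π taken as 3.14 it is 0.002826 cm², as stated.
2. Energy per point: P × t = 0.1 × 10 = 1 J, as stated.
3. Session totals: 10 × 10 s = 100 s and 10 × 1 J = 10 J, as stated.
4. Power density: P/A = 0.1/0.002826 = 35.39 W/cm², against 35.38 stated. The gap is rounding.

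**The figure that does not**

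5. Energy density from energy and area: E/A = 1/0.002826 = 353.9 J/cm².
6. Energy density from the stated power density and time: 35.38 × 10 = 353.8 J/cm².
7. Ratio to the stated value: 353.9/25 = 14.15.

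**Attempts to recover 25 J/cm²**

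| Reading | Arithmetic | Result |
|---|---|---|
| Total energy over the area of all ten spots | 10/(10 × 0.002826) | 353.9 J/cm² |
| All ten points on a single spot | 10/0.002826 | about 3,539 J/cm² |
| Keep 1 J and 25 J/cm², solve for area | 1/25 | 0.04 cm² (diameter about 2.26 mm, against a 0.6 mm fibre) |
| Power density at that area | 0.1/0.04 | 2.5 W/cm², not 35.38 |
| Keep 35.38 W/cm² and 25 J/cm², solve for time | 25/35.38 | 0.71 s, not 10 s |
| Energy per point in that case | 25 × 0.002826 | 0.07 J, not 1 J |

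Every route to 25 J/cm² breaks at least one other stated figure. An area of 0.04 cm² preserves power, time and energy but contradicts the stated spot and power density. The stated spot and power density can be kept only by giving up the stated time and energy.

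**The case against.** The strongest reply is that the delivery variables are clear. Device, wavelength, power, fibre, contact, seconds per point, joules per point, number of points and session totals are all given and agree with each other, and the sham arm mirrors the timing. On this view a single descriptive figure is off, and a reader could recompute the fluence from the rest. The discrepancy leaves randomisation, blinding, the primary endpoint, the sample size and the analysis untouched.

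Much of this stands, and it limits the point in four ways.

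- A reader might infer that the intervention is undefined by a factor of 14. It is not: delivered energy and time are stated consistently, and only the energy density, or the area behind it, is in doubt.
- A reader might infer that the operator could deliver about 0.07 J in place of 1 J per point by setting the device in J/cm². Nothing in the article says that it is set that way; the only operating instructions in the text are seconds, joules and points. The 0.71 s and 0.07 J above show the size of the contradiction and do not predict what will be delivered.
- A reader might infer that comparison with the cited intrusion study, which section 2.12 references for its parameters, is blocked. That study's spot, energy and fluence are not in the documents, so this cannot be judged.
- Table 1 may repeat the 25 J/cm² or may give another beam area. No error can be attributed to it unseen.

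What the reply does not remove is the contradiction itself. The recomputation a reader would do depends on the spot area, and that is one of the two quantities in doubt. Nor is this a detail left to a fuller document, because the article states both densities.

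**Conclusion.** The point holds as an internal contradiction in section 2.12. On the stated power, spot area, time and energy, the energy density is about 354 J/cm² per point, and the stated 25 J/cm² is lower by a factor of about 14. Equivalently, the irradiated area is either the stated 0.002826 cm² or the 0.04 cm² that 25 J/cm² implies at 1 J. Only the usual definitions are assumed: energy density as energy over irradiated area, and power density as power over the same area. No figure from outside the article is used.

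The consequence is that the reported fluence of the experimental treatment would be unreliable. The randomised comparison of the treatment actually delivered remains interpretable. The arithmetic alone does not show which stated figure is in error.

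**What to change.** The investigators should take one stated beam area at the tissue and derive power, area, time, energy, energy density and power density from it, so that all six agree in section 2.12, and in Table 1 if it repeats them. They should establish which figure is in error, for example from the device documentation, and confirm before irradiation that the device setting matches the reconciled values. This review does not propose a value.

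The cost is a correction to one passage, possibly one table, and one check of the device. Nothing in the design, sample size or analysis changes.

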**Table 1 T1:**
[figure not shown]
Photobiomodulation parameters.

**Figure 2 F3:**
[figure not shown]
Laser application on buccal surface of the inclined molar.

Patients in Group 1 (Control) will receive the photobiomodulation placebo, that is, the same treatment performed in Group 2 to mimic the laser application, but with the laser off at the time of application. Group 2 procedures will be performed immediately after the application of forces (placement of elastic bandages) on the tooth, as described:

Simulations will be performed with the same laser (Therapy XT - ANVISA RDC Standard 185/2001 - DMC, São Paulo, SP, Brazil). This will require 10 seconds of application simulation per point. As 10 points will be simulated, it will take 100 seconds for this simulation.The laser beep will be recorded to simulate its operation. Thus the patient will be blind to this procedure. The only person who will know the identity of the groups will be the person applying the laser. The rest of the researchers will not know the interventions made in the groups.The laser head will be positioned perpendicular to the lip in direct contact with the upright tooth mucosa. 5 points will be irradiated by buccal and 5 points by lingual, following the long axis of the tooth that will undergo the movement, being: 2 points in the cervical third, 2 points in the apical third, and 1 in the middle third (Fig. 2).During laser application both, patient and operator, will wear goggles.The laser will be applied immediately (T0) after the mini-implant and lingual button placement procedure, joined by the elastomeric chain ligation, 3 (T1) and 7 (T2) days later. After 30 days, the elastomeric ligature will be changed (therefore, renewal of the vertical force) and this same protocol will be applied (at times T0, T1 and T2). This same elastic bandage change will also occur 60 days after the mini-implant installation, and again the laser application protocol will be followed. Finally, 90 days after baseline, the mini-implant will be removed, as will the lingual button of the molar mesial, but without further laser application.

### Study variables

2.13

The primary variable of the study will be

Radiographic measurements to assess movement rate through tooth angulation vs time at baseline and the final of the treatment.

The secondary variables of the study will be:

Oral health-related quality of life (HRQoL) will be assessed using the OHIP-14 baseline questionnaire applied at baseline and 90 days after treatment.Assess pain during orthodontic verticalization movement using the Visual Analog Scale (VAS) at baseline 30, 60, and 90 days after mini-implant placementAssess the amount of painkillers ingested in the period to verify that this therapy is effective in reducing pain during baseline orthodontic movement, 3 and 7 days, 30, 60, and 90 days after mini-implant placement.evaluation of IL-6, IL-1β, IL-8, TNF-α and IL-10 cytokines by baseline (T0), 3 (T1) and 7 days (T2), and then only in T1 (on 30 and 60 days).

*Movement rate* - With the aid of a ruler (Morelli, Sorocaba, SP, Brazil) and a protractor (transparent Waleu 10290001), an initial panoramic radiography will be compared to a final panoramic radiography (on day 90th) to ascertain the amount (in degrees) of verticalization. By draw a mandibular line (where 1 end would be the lower posterior part of the right goniaco angle region and the other its corresponding left side) and the long axis of the tooth,^[45]^ forming an angle (the larger, the larger the inclination of the tooth). These measurements will be recorded in degrees in each patient's chart for further analysis.

*Pain during movement* - Will be assessed by applying the visual analog scale (VAS) with a 100 mm line, with both ends closed. One end has the indication “0” and the other “100” which means “no pain” and “unbearable pain” respectively. Marking instructions will always be given to the patient by the same operator. Each patient will be instructed to mark with a vertical stroke the point that best corresponds to the pain intensity at the moment of evaluation.^[46]^

*Rescue medication* - Another parameter analyzed will be the amount of analgesics ingested, as proposed by Bauer 2013.^[47]^ At the beginning of the research, a paracetamol (drug with purely analgesic effect^[48]^) card will be delivered to each patient. It should be stored until the end and its use will be released only in case of pain. At the end of the experiment, the number of pills will be evaluated as another parameter to measure pain. This data will be collected by an auxiliary.

*Analysis of oral health-related quality of life (Oral health impact profile questionnaire - Ohip-14)* - This questionnaire is a simplified form of the original OHIP-49 questionnaire. Ohip-14 will be used to assess the impact of oral health on the quality of life of research participants.^[49]^ Ohip-14 is used to measure perceived needs. It measures the impact of oral changes on oral health related quality of life. The participant will answer 14 questions by giving their answers the values 0 (never), 1 (almost never), 2 (sometimes), 3 (most of the time) and 4 (always).

It can be analyzed from 2 perspectives:

Additive method - Points are summed (0–56), with 56 being the biggest impact on quality of life.Domain Assessment - OHIP-14 has a total of 7 domains, which can also be scored from 0–4, with 4 being the biggest impact. To arrive at the result, the 2 questions of each domain are summed and divided by 2. Domain 1 refers to functional limitation, domain 2 refers to physical pain, domain 3 refers to physical limitation, domain 4 refers to psychological discomfort, domain 5 refers to psychological disability, domain 6 refers to social discomfort domain 7 refers to general disability (Table 2).

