### Pretreatment evaluations

2.7

The patients will sign the Informed Consent Form Supplemental Digital Content (ANNEX 1) and the anamnesis Supplemental Digital Content (ANNEX 2) and the OHIP-14 questionnaire Supplemental Digital Content (ANNEX 3) will be applied. A form will be given to the patient to note the time and amount of medication taken. These data will be collected by 1 trained researcher (according to item.2.2 ’Researcher calibration’). Crevicular gingival fluid (CGF) will also be collected by this same professional. And also, the assessment of the impact of oral health on quality of life (OHIP-14). The visual analog scale will be applied immediately before the start of the procedure and will be asked about the amount of painkillers in the last week prior to the surgical procedure. Then the treatment will be performed as randomized by the researcher with dental training, specialist in orthodontics, responsible for the treatment.

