### Experimental design

2.10

Immediately before photobiomodulation (PBM) the responsible researcher will remove and open 1 envelope (without changing the numerical sequence of the other envelopes) and perform the indicated procedure. Thus, the 34 patients will be allocated to the experimental and control groups (considering a 20% drop out) as follows:

G1- Control group (n = 17) - Molar verticalization + laser simulation (placebo) - the treatment of molar verticalization adjacent to tooth loss will be performed with the use of mini-implants for skeletal anchorage (described in detail in the item “2.11 - Orthodontic verticalization mechanic and placement of the mini-implant”), followed by simulation of laser use, since it will be off, being applied at the same points and in the same period of the group that will be irradiated. To mimic the laser action the noise of the BIP will be recorded. Laser mimicking will occur immediately, 3 and 7 days after placement of the mini-implant, and the same sequence will be applied 30 and 60 days after force application (elastomeric ligature replacement), 5 points for buccal and 5 points for lingual. The analgesic pack will be delivered to the patient who will be advised to use only in case of pain. Visual analog scale (VAS), initial molar inclination (panoramic radiography), number of analgesics in the last 10 days, quality of life questionnaire (OHIP-14) and CGF collection will be assessed at baseline. Pain and use of rescue medication will be evaluated in all sessions. CGF collection will always be performed on the second day of laser application in the 3 months of research (totaling 3 collections, outside the baseline) and the questionnaire (OHIP) after 90 days. Another panoramic radiograph will be solicited before the removal of mini-implant (after 90 days).

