G2- Experimental group (n = 17) Molar verticalization + PBM (n = 17 + 3) - the treatment of molar verticalization adjacent to tooth loss will be performed with the use of mini-implants for skeletal anchorage (described in detail in the item “2.11 - Orthodontic verticalization mechanic and placement of the mini-implant”), followed by the use of laser. Immediately 3 and 7 days after surgery, the same sequence was applied 30 and 60 days after force application (elastomeric ligature change), 5 points for buccal and 5 points for lingual, following the long axis of the tooth. The analgesic pack will be delivered to the patient who will be advised to use only in case of pain. Visual analog scale, initial molar inclination (panoramic radiography), number of analgesics in the last 10 days, quality of life questionnaire (OHIP-14) and CGF collection will be assessed at baseline. Pain and the use of rescue medication will be evaluated in all sessions. CGF collection will always be performed on the second day of laser application in the 3 months of research (totaling 3 collections, outside the baseline) and the questionnaire OHIP-14 after 90 days. Another panoramic radiograph will be requested before the removal of mini-implant (after 90 days). (Fig. 1 )

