When working with PBM, the wavelength commonly used and with positive results is around 780 nm^[74,75]^ and 808 nm,^[40]^ that is, in the infrared range, which is the longest. penetration into human tissues.^[24]^ Of the few studies that sought to approach PBM during orthodontic movement, 2 had promising results: Fernandes, 2019,^[40]^ who worked with intrusion movement and wavelength 808 nm. Fernandes 2019^[40]^ had the laser application occurring monthly, always after the application of the forces. This frequency in Fernandes, 2019,^[40]^ can be explained by the fact that the elastomeric chains undergo degradation and loss of almost 76% of the amount of force after 21 days.^[76]^ In addition, numerous studies have shown that the ideal strength range for orthodontic movement ranges from 100 to 450 g.^[61]^ Petrey, 2010,^[77]^ stated that in implants up to 6 mm, the point of failure starts at 461gr of force. To ensure greater stability of the mini-implant in posterior mandibular region, forces less than 2N (200grs) applied immediately and a diameter larger than 1.0 mm are indicated.^[78]^

To analyze the effectiveness of a new method, pain and cytokine analysis are important markers. As subjective as it may be, pain can be measured by counting the number of analgesics consumed during the research^[47]^ and by applying the Visual Analog Scale (VAS), being a way to better interpret and understand the patient's pain, facilitating care planning and decision making, making care more humane and responsive to patient needs.^[46]^

Cytokines, on the other hand, are important inflammatory markers, and as proposed by Kinney, 2014,^[39]^ can be obtained from the manipulated site through crevicular gingival fluid (CGF), which can be easily collected with the help of delicate stems and which carries biological molecular markers collected from the inflamed periodontium.^[39]^

Finally, to analyze the tooth movement rate, tracings made on an initial and final panoramic radiography (after 3 months) will be performed following the model proposed by Ursi, 1990,^[45]^ to analyze dental angulation. It draws a mandibular line (which does not change because it is based on the bony base rather than the occlusal plane) and the long axis of the tooth^[45]^ forming an angle (the larger, the larger the inclination of the tooth). This is the simplest, fastest, most affordable method with the least radiation exposure to the patient.^[45,79]^

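### Section 2.13 lists VAS pain only at baseline and days 30, 60 and 90, while 2.10 has pain assessed at every session; if 2.13 governs, the endpoint omits all six visits 3 and 7 days after a force application

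*Protocol article*

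**What the plan says.** Section 2.13 (Study variables) makes pain during the movement a secondary variable, measured "using the Visual Analog Scale (VAS) at baseline 30, 60, and 90 days after mini-implant" placement. The scale is momentary: the patient marks "the point that best corresponds to the pain intensity at the moment of evaluation". The baseline score precedes treatment, according to 2.7: "The visual analog scale will be applied immediately before the start of the procedure".

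Section 2.10 (Experimental design) gives a different schedule. For the control arm: "Pain and use of rescue medication will be evaluated in all sessions". For the laser arm: "Pain and the use of rescue medication will be evaluated in all sessions".

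Section 2.12 fixes the sessions within a cycle: "The laser will be applied immediately after orthodontic force application (T0), 3 (T1) and 7 (T2) days later". A second cycle then follows on the same pattern, starting with a new elastic: "After 30 days, the elastomeric ligature will be changed (therefore, renewal of the vertical force) and this same protocol will be applied". The cycle is repeated at day 60, and at day 90 the mini-implant is removed with no further laser. Section 2.4 counts 10 appointments in three months.

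For two other secondary variables, 2.13 does list days 3 and 7: the amount of analgesic taken (baseline, days 3, 7, 30, 60 and 90) and the cytokines.

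**The concern.** Pain reduction is one of the aims stated at the end of the Introduction. An analyst looking for the definition of the pain variable would go to 2.13 and find four time points. One precedes treatment. The other three are the days on which an elastic ends its 30-day cycle. The visits at which force was recently renewed and laser or sham is being given are absent, although patients attend them and 2.10 has pain recorded there.

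Two things are at stake. First, if the 2.13 list is used, a finding of no difference in pain would say little about the week after each activation. Second, while both schedules stand, the set of VAS times that forms the endpoint is not fixed and could be settled after the scores are known.

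**Working it through.** **Reproducing the visit count.** Force is applied on days 0, 30 and 60, with laser or sham 0, 3 and 7 days after each application (2.12). Day 90 is the removal visit.

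- 3 cycles × 3 sessions + 1 = 10 visits: days 0, 3, 7, 30, 33, 37, 60, 63, 67, 90. This agrees with the 10 appointments in 2.4, so the reference in 2.10 to all sessions has a definite meaning.

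**The two schedules side by side.**

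- 2.10: all 10 visits.
- 2.13: days 0, 30, 60, 90, which is 4 visits.
- Difference: 10 − 4 = 6 visits, days 3, 7, 33, 37, 63 and 67. These are exactly the +3 and +7 day visits of the three cycles.

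**Time since the previous laser session at the 2.13 times.**

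- Day 30: 30 − 7 = 23 days.
- Day 60: 60 − 37 = 23 days.
- Day 90: 90 − 67 = 23 days.

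The day 90 figure is unconditional, because no laser is given that day. Days 30 and 60 are themselves elastic-change and laser days, so their figures depend on the order within the visit:

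- VAS before the elastic change and laser: all three post-baseline scores come 23 days after the last laser, under an elastic 30 days old.
- VAS after them: days 30 and 60 reflect the moments after new force and laser, and only day 90 has the 23-day gap.

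Under either order, none of the +3 and +7 day visits is covered.

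**Force left in the old elastic.** The Discussion states that "the elastomeric chains undergo degradation and loss of almost 76% of the amount of force after 21 days". Section 2.11 sets the initial force at 150 g. The remainder at day 21 is about 150 × (1 − 0.76) = 36 g, or 24%. The article gives no figure for day 30. This supports the view that an elastic at the end of its cycle exerts much less force; it says nothing directly about pain.

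**Effect on the analysis.** Section 2.14 plans a two-way ANOVA with Bonferroni testing at 0.05. With one between-arm comparison per time point (an assumption; the article does not define the family):

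- 4 time points: 0.05 / 4 = 0.0125 per comparison.
- 10 time points: 0.05 / 10 = 0.005 per comparison.

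The choice of schedule therefore changes the test as well as the data.

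**The case against.** The strongest reply is that 2.10 already has pain recorded at days 3, 7, 33, 37, 63 and 67 in both arms, and that 2.14 speaks of comparing all measurements, so nothing says those scores will be left out. That is fair. What the article shows is two statements that need reconciling, and the harm follows only if 2.13 is the one applied. The objection does not remove the conflict, because 2.13 is where the variables are defined and its list is explicit.

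A reader might infer that the endpoint cannot show any effect on pain, or that no listed VAS falls within 7 days of a force application. The article does not support either. Days 30 and 60 are activation and laser days, and the order of VAS and procedure is given only for baseline.

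A reader might also expect scores near zero in both arms at the listed times. No VAS value or time course of pain appears in the article, and the force-loss figure is used there to explain the laser frequency of an earlier study. Going from low residual force to little pain is an inference.

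Analgesic use is a second pain measure. It is listed at days 3 and 7, and patients note the time and amount taken (2.7), so an early effect could appear there. This is only a partial safeguard: its 2.13 list omits days 33, 37, 63 and 67, and pill use does not measure pain intensity.

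Finally, the VAS list is loosely punctuated and the flowchart is not available here; it may give VAS times. That lowers certainty about what was intended, but the printed text still conflicts.

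**Conclusion.** The contradiction between 2.13 and 2.10 stands. Its size is six of the ten attended visits, comprising every visit 3 or 7 days after a force application. If 2.13 governs, the momentary VAS is poorly placed to show an effect on pain in the week after activation.

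The 23-day gap since the last laser is certain for day 90; for days 30 and 60 it rests on the assumption that the VAS comes before that visit's elastic change and laser. The unstated order is itself a gap to close, since it decides what the day 30 and day 60 scores mean.

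This concerns a secondary variable and leaves the primary movement-rate comparison untouched. It should be corrected before analysis.

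**What to change.** - Align 2.13 with 2.10: make the VAS scores at days 3, 7, 33, 37, 63 and 67 part of the pain endpoint, compared between arms with baseline VAS taken into account.
- State whether the VAS on days 30 and 60 is taken before or after the elastic change and the laser or sham.
- List the rescue-medication time points at the same visits, so that the two pain measures correspond.

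The cost is small. No visit is added, and 2.10 already calls for these scores. The analysis gains time levels and a stricter Bonferroni correction, unless each patient's mean over the chosen visits is compared, which needs a single between-arm test.
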